## Abstract

**Introduction:**

Medicines optimisation is a key role for hospital pharmacists, but with ever-increasing demands on services there is a need to increase efficiency while maintaining patient safety. The aim of this study is to develop a prognostic model, the Medicines Optimisation Assessment Tool (MOAT), which can be used to target patients most in need of pharmacists' input while in hospital.

**Methods and analysis:**

The MOAT will be developed following recommendations of the Prognosis Research Strategy partnership. Using a cohort study we will prospectively include 1500 adult patients from the medical wards of two UK hospitals. Data on medication-related problems (MRPs) experienced by study patients will be collected by pharmacists at the study sites as part of their routine daily clinical assessment of patients. Data on potential risk factors such as polypharmacy, renal impairment and the use of 'high risk' medicines will be collected retrospectively from the information departments at the study sites, laboratory reporting systems and patient medical records. Multivariable logistic regression models will then be used to determine the relationship between potential risk factors and the study outcome of preventable MRPs that are at least moderate in severity. Bootstrapping will be used to adjust the MOAT for optimism, and predictive performance will be assessed using calibration and discrimination. A simplified scoring system will also be developed, which will be assessed for sensitivity and specificity.

**Ethics and dissemination:**

This study has been approved by the Proportionate Review Service Sub-Committee of the National Health Service Research Ethics Committee Wales REC 7 (16/WA/0016) and the Health Research Authority (project ID 197298). We plan to disseminate the results via presentations at relevant patient/public, professional, academic and scientific meetings and conferences, and will submit findings for publication in peer-reviewed journals.

**Trial registration number:**

NCT02582463.

Strengths and limitations of this studyThe Medicines Optimisation Assessment Tool (MOAT) will be the first evidence-based prognostic model to identify hospitalised patients at risk of moderate or severe medication-related problems in order to permit targeting by pharmacists.The study will include adult patients of all ages admitted to all types of medical wards (general, emergency and elderly medicine), so will be representative of patients routinely admitted to hospital medical wards.The method and analysis plan are based on the Prognosis Research Strategy, Transparent Reporting of a multivariable prediction model for Individual Prognosis Or Diagnosis (TRIPOD) and CHecklist for critical Appraisal and data extraction for systematic Reviews of prediction Modelling Studies (CHARMS) recommendations for prognostic research.The study is observational, which may be subject to reporting bias and missing data.Only two hospitals will be included in the study; further validation, impact and implementation studies will be needed to determine whether the MOAT could be successfully employed in new settings.

## Introduction

Medicines play a crucial role in maintaining health and are the most common intervention in healthcare. However, in the UK, as elsewhere, there is a growing body of evidence that there is a need to improve medicines use.^1–6^ This includes the Francis and Berwick reports,^1 2^ which call for a number of actions to improve patient safety and reduce avoidable harm.

Historically, adverse drug events have been the focus of studies of medication-related harm,^7^ but problems can also result from suboptimal medicines use, such as ineffective treatments or subtherapeutic doses. It is estimated that only 4%–21% of patients in primary care receive optimum benefit from their medicines,^8^ and it has been suggested that research efforts should also identify patients with unrealised benefits.^9^ A term that encompasses both aspects is medication-related problems (MRPs), defined as all circumstances involving a patient’s drug treatment that actually, or potentially, interfere with the achievement of an optimal outcome.^7 10–12^ This also shifts the focus from ‘medication-related harm’ to ‘medicines optimisation’, which can be described as the safe and effective use of medicines to enable the best possible outcomes.^5^ Medicines optimisation is high on the English national agenda, with guidance issued by the Royal Pharmaceutical Society and the National Institute for Health and Care Excellence.^4 5^

Medicines optimisation is a key role for pharmacists,^13–16^ and a number of systematic reviews conclude that addition of clinical pharmacy services to the care of hospital inpatients improves quality, safety and efficiency of patient care.^10 17 18^ Ideally, pharmacists would see every patient daily, but medicines optimisation is not the only goal for hospital pharmacy services in England.^13 19^ Other service developments are required, such as delivery of 7-day services^20^ and the Hospital Pharmacy Transformation Programme, as set out in the recent review by Lord Carter on improving productivity and performance in English National Health Service (NHS) acute hospitals.^21^ Owing to financial challenges that face the NHS, these developments often have to be achieved within existing funding through increased efficiency and innovation.^5 22 23^ There have therefore been calls from international government organisations and professional bodies for effective ways for pharmacy services to target patients most in need.^15 24–28^

Clinical prioritisation has been proposed as a way to permit pharmacy services to focus on the greatest need and where clinical pharmacy input is likely to have greatest impact. This requires a method to triage patients to assign ‘pharmaceutical acuity’.^28 29^ There are recognised risk factors for MRPs, for example polypharmacy, renal impairment and the use of ‘high risk’ medicines,^30^ but to target patients appropriately pharmacists need to be able to apply this knowledge effectively and consistently within their routine clinical practice.

Predicting clinical risk is well established in medicine. Tools such as cardiac-risk calculators and the Waterlow score (to assess the risk of pressure ulcers) are both used daily across the NHS.^31 32^ Prediction tools to identify hospitalised patients at risk of adverse medication-related outcomes have been developed,^33–41^ but the majority identify patients at risk of adverse drug reactions,^34 35^ adverse drug events^36^ or medication errors,^37^ rather than MRPs, or are based on ‘expert opinion’ rather than statistical determination.^38–41^

Interest in prediction research (also known as prognosis research) has developed rapidly in recent years. It involves use of statistical methods to predict future health outcomes among people with a given baseline health status, and therefore has potential to inform clinical decision making, improve patient care and make healthcare more efficient.^42 43^ Prognostic modelling is one component of prognosis research, in which multiple risk (prognostic) factors are statistically combined to predict future clinical risk for an individual patient.^44^ However, many published prognostic model studies have been criticised in terms of methodological shortcomings, limiting their reliability and applicability,^44 45^ as well as poor reporting, which limits the ability to effectively assess the risk of bias.^43 46^ Both problems ultimately limit the usefulness of the prognostic models. The perceived inadequacies in prognostic model research prompted the recent publication of recommendations for prognosis research by the Prognosis Research Strategy (PROGRESS) partnership,^42 44 47 48^ together with specific guidelines for reporting^43 46^ and critically appraising^49^ prognostic model research.

This study aims to address a current gap in the evidence base: the development of a methodologically sound prognostic model to target hospital patients most in need of pharmacists’ input based on their risk of MRPs. The purpose of publishing this study protocol is to expand on the details already publicly available^50^ to clearly specify a priori the outcome measure, prognostic factors and analysis plan. This is intended to protect against both data-driven model development (associated with overoptimistic model performance) and selective reporting. The study method is informed by the PROGRESS guidelines, and the protocol includes the key elements proposed by Peat *et al*
43 for inclusion in prognostic model protocols, and follows the Transparent Reporting of a multivariable prediction model for Individual Prognosis Or Diagnosis (TRIPOD) Statement guidance^46^ and the CHecklist for critical Appraisal and data extraction for systematic Reviews of prediction Modelling Studies (CHARMS) checklist^49^ in terms of the level of detail provided. This is to ensure provision of sufficient information to permit full assessment of risk of bias and applicability.

The aim of this study is to develop a prognostic model, the Medicines Optimisation Assessment Tool (MOAT), to identify adult patients at highest risk of preventable, moderate or severe MRPs during admission to a UK medical ward. Additional objectives are to assess the MOAT’s content validity, feasibility of use, potential efficiency savings and the potential clinical risk associated with false-negative predictions. The proposed purpose of the MOAT is to permit appropriate targeting of patients by pharmacy staff in order to reduce risks, improve patient outcomes and increase efficiency of hospital clinical pharmacy services, thereby supporting delivery of national targets related to patient safety, medicines optimisation and service provision.

## Methods and analysis

### Design

This is a prognostic model development study that aims to select candidate predictors (the potential prognostic factors) and combine them into a multivariable model using logistic regression. Internal validation (bootstrapping) will be used to evaluate the performance of the model and permit adjustment for optimism. The MOAT will be developed using a prospective cohort study involving adults admitted to the medical wards at two UK hospitals in South East England. Two study sites, Hospitals A and B, were chosen to increase generalisability of the MOAT as they have markedly different patient demographics. It is anticipated that the study will be completed by April 2018.

### Eligibility criteria

Patients aged 18 years old or over will be selected by means of being consecutive admissions to the medical wards (general, emergency and elderly medicine) at the two study sites during the study period. Patients admitted to other specialties such as surgery, maternity and paediatrics will be excluded due to potential differences in the prevalence/type of MRPs in these patient groups.

Patients will be excluded if:their admission is for investigation only (as changes to medication will be minimal)they are not prescribed any medication during the admissiontheir entire admission is outside of core pharmacy working hours (ie, 09:00–17:00 Monday–Friday) as these patients are unlikely to receive review by a clinical pharmacisttheir prescription is not reviewed by a clinical pharmacist during the admission (eg, a patient who is present on a study ward during core pharmacy working hours but discharged before a clinical pharmacist is able to review his/her medication).

### Outcome

The outcome of interest for the prognostic modelling will be MRPs that are at least moderate in severity and preventable. Research has shown that a significant proportion of hospitalised patients will experience MRPs (eg, Blix *et al*
51 reported a rate of 81%), many of which are of limited clinical significance. We will therefore use moderate or severe MRPs as this will enable the MOAT to target patients most in need of pharmacist input in terms of risk of medication-related harm or suboptimal use. It will also ensure that the MOAT is clinically relevant and feasible to implement in terms of pharmacists’ workload. Similarly, only MRPs considered as ‘preventable’ will be considered to ensure that the MOAT identifies patients with MRPs that are amenable to pharmacist intervention either directly or through discussion with prescribers.

The definition for MRPs that will be used is ‘all circumstances involving a patient’s drug treatment that actually, or potentially, interfere with the achievement of an optimal outcome’.^7 10–12^

All MRPs will be classified for descriptive reporting purposes. As there is no universally accepted classification system and perceived deficiencies with some systems, we will use the aggregated classification system recently developed by Basger *et al*.^52^ This provides a comprehensive classification system based on the causes of MRPs, thereby preventing any potential confusion between MRP ‘causes’ and ‘outcomes’.

MRP data will be identified and recorded by pharmacists at the study sites as part of their routine daily clinical assessment of patients. They will record data on all MRPs identified personally or through discussion with other healthcare professionals. The hospital incident reporting systems will also be reviewed to check for any additional significant MRPs that are not identified by pharmacy staff. Following training on the use of Basger’s aggregated classification system, pharmacists will be asked to classify each MRP at the point of identification.

MRP data will be collected for all study patients from admission to discharge from hospital, or the date the study closes (2 weeks after inclusion of the final study patient), whichever occurs sooner. A study close date will be used to facilitate practicality in terms of data collection, while permitting data to be collected from admission to discharge for the majority of study patients (as the mean length of stay at the study sites is approximately 6 days).

Previous research into the detection of prescribing errors, a subset of MRPs, has shown that the observed incidence is extremely dependent on the method of detection.^53^ We have chosen to use prospective identification by pharmacists for this study because (1) the purpose of the study is to develop a prognostic model for MRPs that can be identified during routine clinical practice by pharmacists; (2) it will permit the identification/inclusion of MRPs that are not routinely recorded in medical notes, such as potential prescribing or administration errors that are intercepted; and (3) it will permit the MRPs to be identified by staff personally involved in the care of the study patients, increasing clinical and practical relevance.

It is acknowledged that a limitation will be the possibility of incomplete data due to pharmacy staff being required to complete this work in addition to other routine duties. To minimise this, the principal investigator will work closely with the study sites to ensure that data collection occurs at an optimal time in terms of staffing levels and workload. Staff involved in MRP data collection will also be provided with initial training to improve the consistency and reliability of data collection. The principal investigator will review all data collection forms daily and seek clarification where needed, and provide the pharmacists with ongoing fidelity training.

We also recognise that identification of MRPs may vary depending on the knowledge, experience and skills of the pharmacists collecting data. To quantify this potential variability, a simulated ‘MRP identification assessment exercise’ will be developed and used in a training scenario. Each simulated MRP will be treated as having a binary outcome in terms of whether or not it is identified by each pharmacist. Fleiss’ kappa will be used to calculate the level of agreement between pharmacists.

In prognostic research it is recommended that the outcome is assessed while blinded to the candidate predictors (potential prognostic factors) to prevent bias.^49 54 55^ In this study it will not be possible to blind the pharmacists collecting the outcome data to the patient’s clinical information (such as age, diagnosis, laboratory results and so on) as this information will form part of their clinical assessment of the patient. Despite this, the pharmacists collecting the outcome data will not know which factors will be used as candidate predictors in order to minimise the potential for this information to influence their outcome assessment.

Following anonymisation to maintain patient confidentiality and blinding, each potential MRP will be assessed by an expert panel. Agreement will be reached by consensus on whether it is a true MRP, and then confirmed MRPs will be assessed for severity. The expert panel will comprise the principal investigator, a hospital pharmacist, a senior nurse and a consultant physician. Once MRPs have been confirmed, the panel will assess each MRP for severity. As no established grading for MRPs is available, severity will be classified using a validated visual analogue scale for medication errors,^56^ used previously for this purpose by Rashed *et al.*
57 MRPs will be scored independently in terms of potential patient outcomes on a scale of 0–10, where 0 represents a case with no potential adverse effect on the patient and 10 a case that would result in death. The mean score for each MRP from the panel members will be used as an index of severity, with a score of less than 3 being considered as a minor outcome (very unlikely to have an adverse effect), a score of 3–7 will be considered as moderate (likely to cause some adverse effects or interfere with therapeutic goals, but very unlikely to result in death or lasting impairment), and a score of greater than 7 will be considered to be a severe outcome (likely to cause death or lasting impairment).

No established grading system for MRP preventability is available; therefore, we considered two possible methods: the criteria provided by Schumock and Thornton,^58^ and the ‘P Method’.^59^ We concluded that both methods were developed for adverse drug reactions, most of which are unpreventable, whereas the majority of MRPs are inherently preventable. Neither method was therefore appropriate for the present study. Pharmacists will therefore be asked to review each MRP at the point of identification to assess whether it was preventable, expressed as a dichotomous variable of yes or no. The principal investigator will then perform a second check of all MRPs to ensure consistency. To prevent ‘judgement drift’ a ‘case law document’ will be used.^60^

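### Fleiss' kappa alone does not isolate the between-pharmacist variability in MRP detection that the simulated exercise is meant to quantify

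*Protocol article*

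**What the plan says.** The Outcome section of the protocol article accepts that "identification of MRPs may vary depending on the knowledge, experience and skills of the pharmacists collecting data". The sentence introducing the exercise states its purpose in its opening words: "To quantify this potential variability, a simulated". The exercise "will be developed and used in a training scenario". On scoring: "Each simulated MRP will be treated as having a binary outcome in terms of whether or not it is identified by each pharmacist". On analysis, Fleiss' "kappa will be used to calculate the level of agreement between pharmacists".

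No other summary of the exercise is named. The article gives no number of pharmacists, number of simulated MRPs, expected detection rate or kappa threshold. Neither the sample size section nor the data analysis plan uses the result.

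**The concern.** The stated aim is a spread: how much detection differs from one pharmacist to another. The named statistic answers a different question, namely whether pharmacists agree item by item more than the pooled detection rate alone would produce. If the scored items are all genuine (simulated) MRPs, agreement beyond chance arises chiefly because some MRPs are easy and others hard. The investigators choose that mix when they build the exercise.

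The aim matters because pharmacist detection is the main route by which the study outcome is measured. The expert panel judges only MRPs that have been put to it, and the incident-report review is a partial backstop. Readers of the final model will want to know how much of the outcome depends on which pharmacist saw the patient. A single kappa could suggest poor consistency among uniform pharmacists, or good consistency among pharmacists who differ.

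**Working it through.** The article states no kappa value, so there is no figure to reproduce. The check asks how kappa responds to pharmacist skill and to item difficulty when each is varied separately. All numbers of pharmacists and items, and all detection rates, are assumptions.

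**Formula.** Kappa = (P − Pe)/(1 − Pe). P is the mean pairwise agreement per item. Pe = p² + (1 − p)², where p is the detection rate pooled over pharmacists and items. Two pharmacists with detection rates a and b on an item agree with probability ab + (1 − a)(1 − b).

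**Step 1: expected values by hand (20 pharmacists).**

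- *Identical pharmacists at 0.95, equal items.* P = 0.95² + 0.05² = 0.905 and Pe = 0.905, so kappa = 0 despite over 90% raw agreement.
- *Half the pharmacists at 0.40, half at 1.00, equal items.* p = 0.70 and Pe = 0.49 + 0.09 = 0.58. Of 190 pairs, 45 are low-low (agreement 0.52), 45 high-high (1.00) and 100 mixed (0.40). P = (45×0.52 + 45×1.00 + 100×0.40)/190 = 108.4/190 = 0.5705. Kappa = (0.5705 − 0.58)/0.42 = −0.02.
- *Identical pharmacists, 70% of items found at 0.95 and 30% at 0.1167.* p = 0.665 + 0.035 = 0.70 and Pe = 0.58. P = 0.7×0.905 + 0.3×(0.1167² + 0.8833²) = 0.6335 + 0.2382 = 0.8717. Kappa = (0.8717 − 0.58)/0.42 = 0.69.

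Uniform pharmacists therefore give 0 or 0.69 depending only on the items, and very unequal pharmacists can give about 0.

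**Step 2: simulation, 10 pharmacists and 30 MRPs, 4000 exercises per setting.** The logit of detection is 1.735 (85%) plus a pharmacist effect (SD 0 or 1) plus an item effect (SD 0 or 1.5). A pharmacist SD of 1 puts the range of ±1.5 SD at logits 0.235 to 3.235, that is, about 56% to 96%.

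| Items | Pharmacists | Mean kappa | SD of pharmacists' observed detection rates |
|---|---|---|---|
| Equal | Identical | 0.00 | 0.06 |
| Equal | About 56-96% | −0.02 | 0.15 |
| Varied | Identical | 0.24 (5th-95th percentile 0.11 to 0.38) | 0.06 |
| Varied | Same spread | 0.19 (0.08 to 0.32) | 0.14 |

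Mean detection is about 81-85% in the equal-item rows and 75-78% in the varied-item rows. The SD of 0.06 for identical pharmacists is sampling noise from 30 items. The two kappa ranges in the varied-item rows overlap almost entirely, so one exercise could hardly tell the two situations apart. The SD of detection rates roughly doubles.

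**Step 3: same pharmacist spread, different items (20 pharmacists, 200 items, skill spread ±1.5 logits).** With the easy/hard mix of Step 1, kappa is 0.61. With equal items it is −0.01. The pharmacists are the same in both.

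**Step 4: fixed item distribution, widening skill (10 pharmacists, 30 items).** With item SD 1.5, pharmacist SDs of 0, 1 and 2 give kappa 0.24, 0.19 and 0.11. With item SD 3 they give 0.52, 0.46 and 0.35. Kappa does fall as skills diverge, but its level is set by the items: the most divergent pharmacists on the second set (0.35) score above identical pharmacists on the first (0.24).

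**The case against.** The strongest defence is that the sentence on kappa promises only a level of agreement, and Fleiss' kappa is a recognised chance-corrected index of that for several raters and a binary rating. That stands: kappa is a legitimate agreement statistic. But the article gives the purpose of the exercise as quantifying variability due to pharmacists, and for that purpose kappa alone is a poor match.

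A second defence is that there will be one exercise with one item set, and on a fixed set kappa does fall as skills diverge (0.24 to 0.11 in Step 4). This also stands, and it rules out saying that kappa is insensitive to skill. It does not make the single value readable, because the investigators will have no kappa for identical pharmacists on their own item set to compare it with. The equal-difficulty rows are a limiting case that nothing in the article suggests; the varied-item rows are the more realistic ones.

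Third, a reader might infer that the exercise cannot deliver the figure it is planned for. The article does not support that: the found/not-found table of pharmacists by MRPs already holds every pharmacist's detection proportion. A reader might also infer that a low-detecting pharmacist would go unnoticed. That assumes nobody looks at individual results, which the article does not say. It also describes initial training, daily review of forms by the principal investigator, ongoing fidelity training and a review of incident reports.

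Finally, that only simulated MRPs are rated is an inference from the scoring sentence, since the exercise had still to be developed. Naming one statistic in an article does not rule out descriptive detection rates, but it does make kappa the stated answer to the stated aim.

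**Conclusion.** The point holds in a limited form. Fleiss' kappa on found/not-found scores of simulated MRPs does not isolate between-pharmacist variability in detection. It depends mainly on the difficulty mix of the exercise and weakly to moderately on pharmacist skill. Under the assumed settings, moving from identical pharmacists to a 56-96% spread shifts kappa by 0.02 (equal items) or 0.05 (varied items), while the SD of detection rates rises by 0.08 to 0.09.

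The sizes rest on assumed numbers of pharmacists and items, and on assumed detection rates and spreads; the direction does not depend on the particular values tried. The fault is in the choice of sole summary, not in the exercise. Severity is low: the article gives kappa no threshold, no decision, and no role in the sample size or the model.

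**What to change.** Replace the sentence on kappa with one saying that, from the same exercise data, the study will report each pharmacist's detection proportion with its 95% CI and the spread across pharmacists (SD and range), with Fleiss' kappa as a secondary index of agreement. Because part of the observed SD is sampling noise from a finite number of items, state the number of simulated MRPs next to it.

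Optionally, add a pharmacist variance component from a logistic model with crossed random effects for pharmacist and MRP. It separates skill from item difficulty, but will be imprecise with few pharmacists and should be reported with that caveat.

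The cost is one sentence and a short table, with no new data and no extra work for the pharmacists.
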